### Outcome measures

#### Primary outcome.

**Balance**. Balance performance will be assessed using the Mini-Balance Evaluation Systems Test (Mini-BESTest). This tool evaluates both static and dynamic balance impairments and identifies the risk of falls. It includes 14 items grouped into 4 domains: anticipatory postural adjustments, reactive postural control, sensory orientation, and dynamic gait. Each item will be evaluated on a 3-point ordinal scale ranging from 0 to 2, where 0 denotes minimal functional performance and 2 denotes optimal function. The total score can reach a maximum of 28 points, representing the absence of risk of falls [37]. The Mini-BESTest has demonstrated excellent test-retest reliability in individuals with PD [38,39].

#### Secondary outcomes.

**Functional mobility**. Functional mobility will be assessed using the Timed Up and Go test (TUG). From a seated position in a chair with armrests, participants will be instructed to stand up, walk 3 meters, turn around, return to the chair, and sit down [40]. A result of more than 12 seconds will be indicative of a risk of falls [41]. The TUG has demonstrated high interrater reliability in individuals with PD [42].

To assess mobility under cognitive load, the Timed Up and Go Dual Task (TUG-DT) will be used. Participants will follow the same procedure as in the TUG, but while walking, they will simultaneously perform a cognitive task (e.g., counting backward from 70 in steps of 3). A result of more than 14,7 seconds will be indicative of a risk of falls [41]. This test will evaluate functional mobility in dual-task conditions [43].

**Gait Speed**. Gait speed will be measured using the 10-Meter Walk Test (10MWT). Participants will be instructed to walk 10 meters on a flat surface, performing 3 trials at a comfortable walking speed and 3 at a fast-walking speed. The average speed (in meters/second) for each condition will be calculated. Speeds below 1.1–1.2 m/s would indicate a higher risk of falls [44]. This test has shown excellent test-retest reliability at a comfortable pace in individuals with PD [45].

**Lower limb strength**. Lower limb strength will be evaluated using the 30-Second Sit-to-Stand Test (30CST), which is part of the Senior Fitness Test (SFT) [46]. Participants will be seated on a chair with their back straight, feet flat on the floor, and arms crossed over their chest. They will be asked to complete as many full sit-to-stand movements as possible within 30 seconds [47]. The 30CST has demonstrated excellent test-retest reliability in community-dwelling older adults [48].

**Quality of life**. Health-related quality of life will be measured using the Parkinson’s Disease Questionnaire-39 (PDQ-39). This self-administered instrument consists of 39 items distributed across 8 dimensions and will assess quality of life during the previous month in individuals with PD. Each item is scored on a 5-point ordinal scale ranging from 0 (never) to 4 (always). The scores for each dimension are averaged and transformed to a scale of 0–100, where 0 represents the best possible quality of life and 100 the worst. Lower values will indicate a better perceived quality of life, and higher values will reflect a greater impact of the disease [49]. The PDQ-39 has demonstrated high test-retest reliability [50].

**Adverse symptoms**. Adverse symptoms related to IVR exposure will be monitored using the Simulator Sickness Questionnaire (SSQ). This questionnaire includes 16 items across 3 domains: oculomotor symptoms, nausea, and disorientation. Symptoms will be scored for intensity and interpreted as follows: < 5 = insignificant, 5–10 = minimal, 10–15 = significant, 15–20=concerning, and >20 = severe [51]. This questionnaire will also serve as a criterion for discontinuing participation in the IVR physical therapy program. Participants who score 20 will be withdrawn from the study, as this reflects the presence of severe symptoms identified by the scale. The SSQ has demonstrated good internal consistency [52].

**Satisfaction**. Participant satisfaction with the intervention will be assessed using an *ad hoc* one-question questionnaire developed for this clinical trial. Responses will be recorded on a 5-point Likert scale, where 1 will indicate “very dissatisfied” and 5 will indicate “very satisfied.”

**Adherence**. A participant’s adherence will be evaluated based on attendance records during the intervention phase. Individuals were categorized as showing *high adherence* when they attended no fewer than 80% of the scheduled sessions and completed all prescribed exercises or more. In contrast, *non-adherence* was defined as attending fewer than 20% of the total sessions planned [53].

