### Eligibility criteria

Before inclusion in the study, all potential participants will be fully informed about the study and asked to provide written informed consent. The inclusion criteria will be: 1) Patients diagnosed with PD by a neurologist; 2) Aged 55–90 years and classified as stages 2,5–4 on the modified Hoehn & Yahr scale; 3) Independent in standing and walking, with or without technical aids; 4) A score >24, as evaluated using the validated Spanish version of the Mini-mental State Examination (MMSE-MEC) [32]. The exclusion criteria included will be: 1) Visual or auditory disturbances that make it difficult to perceive the information provided or may cause vertigo or epilepsy; 2) Musculoskeletal disorders or pathological conditions limiting the ability to perform exercises; 3) Psychiatric disorders such as moderate or severe depression, as well as impulse control disorders diagnosed in the last year. The withdrawal criteria will be: 1) Occurrence of severe adverse effects during IVR use, defined as a Simulator Sickness Questionnaire (SSQ) score greater than 20; 2) Voluntary withdrawal by the participant.

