**Exercise 7. Striding**	Dynamic balance	Increase gait complexity + base of support	Striding. The physical therapist will indicate whether you should keep your eyes open or closed. Repeat the exercise as many times as necessary until you reach a new level.	Striding with eyes open.	Striding with eyes closed.	Striding following a straight line with eyes opened.	Striding following a straight line with eyes closed.
**Exercise 8. Walking with pelvic–shoulder dissociation**	Dynamic balance	Motor-cognitive dual task + gait challenge	Walking with pelvic-shoulder dissociation with two poles (spikes). The physical therapist will give you instructions on whether to do this with your eyes open or closed. Repeat the exercise as many times as necessary until you reach a new level.	Normal walking with two poles that you will move alternately.	Normal walking with two poles that you will move alternately with your eyes closed.	Walk in semi-tandem with two poles, moving them alternately while following a line with your eyes open.	Walk in semi-tandem with two poles, moving them alternately while following a line with your eyes closed.

To ensure participant safety and prevent falls, all intervention sessions will be conducted under continuous one-to-one supervision by an experienced physical therapist. The physical therapist will remain nearby at all times, will monitor task execution, and will provide immediate physical assistance in the event of balance loss.

For participants in the experimental group, the physical therapist will administer the SSQ immediately at the end of each session to monitor potential adverse effects associated with IVR exposure, including nausea, oculomotor discomfort, dizziness, and disorientation. SSQ scores and any reported symptoms will be systematically recorded. If relevant symptoms are detected, the session will be paused, and persistent or severe symptoms will result in discontinuation of the intervention and documentation as adverse events. Any adverse events occurring in the control group will be also monitored and reported during the study.

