### Sample size calculation

Sample size estimation was performed using G*Power software (version 3.1.9.7), taking the primary outcome variable, balance, assessed by the Mini-BESTest scale as the reference. Although the hypothesis anticipates superior outcomes for the experimental IVR intervention compared to the control condition, a two-tailed alternative hypothesis was adopted to maintain a conservative statistical approach. The calculation was based on a repeated measures design involving two groups and three time points, but specifically on the expected difference between groups at the post-intervention time point assuming a moderate effect size (d = 0.71), a significance level of 0.05, and a statistical power of 80%**.** Although the study includes follow-up measurements, this approach provides a conservative estimate expected to offer adequate power for comparisons at follow-up. Because the sample size calculation relies on the expected between‑group difference at the post‑intervention time point, assumptions about the correlation between repeated measurements will not be necessary. Under these conditions, the required sample size was determined to be 50 participants, with 25 allocated to each group. To accommodate an estimated 10% attrition rate, the final target sample was increased to 56 participants (28 per group).

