### Statistical analysis

Statistical analysis will be performed with Statistical Package for the Social Sciences version 29.0 (SPSS Inc, Chicago, IL). The significance level will be 0.05 for all statistical analyses. Descriptive statistics will summarize participants’ baseline characteristics and study outcomes. Categorical variables will be presented as absolute and relative frequencies (n, %), whereas continuous variables will be expressed as mean ± standard deviation or, when appropriate, as median and interquartile range, together with 95% confidence intervals. The Shapiro–Wilk test will assess the normality of continuous variables. To ensure comparability between groups at baseline, appropriate parametric or nonparametric tests will be applied depending on data distribution: t-tests or Mann–Whitney U tests for continuous data, and Chi-square tests for categorical data.

To examine the effects of the intervention across time, linear mixed-effects models will be employed to analyze group‑by‑time interactions across the three measurement points. Significant main or interaction effects will be further explored through Bonferroni-adjusted post hoc comparisons. In cases where data deviate from normality, within-group changes will be analyzed using the Friedman test, followed by Wilcoxon signed-rank tests for pairwise comparisons. Bonferroni correction will be applied to control for multiple testing and Type I error.

Between-group differences at each time point will be examined using independent-samples t-tests (accompanied by Levene’s test for homogeneity of variances) for normally distributed data, or Mann–Whitney U tests for non-parametric data. Categorical outcomes will be compared using Chi-square or Fisher’s exact test, as appropriate.

All analyses will follow the intention-to-treat (ITT) principle, including every randomized participant in the group to which they were initially assigned, regardless of adherence, or protocol deviations. Missing data will be managed through suitable statistical procedures, such as last observation carried forward (LOCF) or multiple imputation, depending on the type and extent of missingness.

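### A high SSQ score is written as withdrawal from the study and not only from IVR, so outcomes are lost in one arm for a treatment-related reason

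*Protocol article*

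**What the plan says.** The protocol article attaches two different consequences to a high SSQ score.

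- **Secondary outcomes, Adverse symptoms**, on the programme: "This questionnaire will also serve as a criterion for discontinuing participation in the IVR physical therapy program".
- **The next sentence of that paragraph**, on the study: "Participants who score 20 will be withdrawn from the study, as this reflects the presence of severe symptoms identified by the scale".
- **Intervention**, on treatment again: "persistent or severe symptoms will result in discontinuation of the intervention and documentation as adverse events".
- **Eligibility criteria**, first withdrawal criterion: "Occurrence of severe adverse effects during IVR use, defined as a Simulator Sickness Questionnaire (SSQ) score greater than 20". It does not say what the participant is withdrawn from. The only other item in the list is the participant's own decision to leave.

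The questionnaire is described for one arm: "For participants in the experimental group, the physical therapist will administer the SSQ immediately at the end of each session". Control-arm adverse events are monitored and reported, with no score threshold.

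For analysis, the Statistical analysis section states: "All analyses will follow the intention-to-treat (ITT) principle, including every randomized participant in the group to which they were initially assigned". Missing data are to be handled by methods "such as last observation carried forward (LOCF) or multiple imputation, depending on the type and extent of missingness".

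**The concern.** A sickness stop that applies only to headset users is reasonable. The defect is that the stop also ends study participation. Stopping the headset protects the participant; cancelling a later balance assessment does not.

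If the sentence is followed as written, outcomes go missing in one arm only, and they go missing because participants could not tolerate the treatment under test. People who tolerate IVR badly may also respond differently to it, so the participants left in the IVR arm are no longer comparable with the full control arm. Keeping the withdrawn participants in the intention-to-treat set by name does not supply their outcomes. These would have to be modelled, carried forward from baseline, or imputed.

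**Working it through.** **Timing.** The Intervention section gives 8 sessions over 4 weeks, then a follow-up at 3 months. The SSQ follows each session, so there are 28 × 8 = 224 planned SSQ occasions in the IVR arm, all before the post-intervention assessment. The Sample size calculation rests "specifically on the expected difference between groups at the" post-intervention time point. A study withdrawal triggered at any session therefore removes both post-baseline outcomes, including the one that sizes the trial. A score above 20 after session 8 shows the problem most clearly: no IVR exposure remains to be stopped, yet the participant would still leave the study.

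**The plan's own attrition figure.** 50 / (1 − 0.10) = 55.6, rounded up to 56, or 28 per arm. This reproduces. The allowance is 28 − 25 = 3 participants per arm.

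**Inputs for the illustration.** The article gives 28 per arm and d = 0.71. It gives no rate of SSQ above 20. The figure cited in the Discussion (at least one adverse symptom in 8.5% of 1012 sessions) carries no severity grade. The following are therefore assumptions:

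- k = number of IVR participants withdrawn on SSQ, 1 to 3 (3 uses the arm's whole allowance);
- D = how far below IVR completers they would have scored, beyond what baseline explains, 0.5 to 1.0 SD;
- G = the change from baseline they would have shown, +0.5 to −0.5 SD.

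**Completer or missing-at-random analysis adjusted for baseline.** Bias = +(k/28) × D.

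| k | k/28 | D = 0.5 SD | D = 1.0 SD |
|---|---|---|---|
| 1 | 0.036 | +0.018 | +0.036 |
| 2 | 0.071 | +0.036 | +0.071 |
| 3 | 0.107 | +0.054 | +0.107 |

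As a share of the planned effect: 0.018 / 0.71 = 2.5% and 0.107 / 0.71 = 15%. The direction favours IVR if poor tolerators would have done worse.

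**LOCF, which here carries baseline forward.** Bias = −(k/28) × G. At k = 3:

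- G = +0.5: −0.107 × 0.5 = −0.054 SD, against IVR;
- G = −0.5: −0.107 × (−0.5) = +0.054 SD, towards IVR.

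A harsher case lies outside that range of G. With no true effect, a common gain of 0.3 SD and D = 1.0, G = 0 + 0.3 − 1.0 = −0.7, and the bias is 0.107 × 0.7 = +0.075 SD. So the sign under LOCF depends on what the withdrawn participants would have done, which cannot be observed once they have left.

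**The cut-off.** The Adverse symptoms paragraph withdraws at a score of 20. Its own bands put 15–20 in the concerning category and only values above 20 in the severe one, and the Eligibility criteria also use above 20.

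**The case against.** The strongest counter-argument is that loss of outcomes is inferred. The article nowhere says that assessments cease after an SSQ stop; two of the statements describe stopping treatment; and the analysis section keeps every randomised participant. The study-withdrawal sentence may be loose wording, and the full protocol may set out the visits that follow discontinuation. It stands that the article does not expressly cancel the assessments. But leaving the study is the plain meaning of the sentence, nothing shown says a stopped participant is still assessed, and site staff could follow either version. This is an explicit statement in conflict with its neighbours, so condensation into an article does not explain it.

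The bias figures rest wholly on assumptions. That is correct. At k = 1 and D = 0.5 the bias is negligible, and the upper end needs the arm's entire allowance plus a full 1 SD shortfall. Familiarisation, session pauses and optional breaks should also keep k low, and Strengths and limitations describes withdrawal through IVR side effects only as a possibility.

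Multiple imputation could use the recorded SSQ scores. This helps in part, but if everyone above the cut-off leaves, no outcomes are observed there and the imputation extrapolates.

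Finally, recruitment was due to end in February 2026 and data collection in May 2026, so a change helps only participants with assessments still ahead. That limits the benefit without removing it.

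**Conclusion.** The concern holds and should be fixed. The conflict between leaving the study and leaving the IVR programme is certain from the text. If the study-withdrawal sentence is followed, the primary and 3-month outcomes are lost in the IVR arm only, for a reason caused by the treatment, and the stated missing-data methods do not reliably correct for this.

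The size cannot be determined from the article. Under the assumptions above it is +0.02 to +0.11 SD for a completer or missing-at-random analysis, and −0.05 to +0.05 SD under LOCF with 3 withdrawals and G within ±0.5 SD. The difference between 20 and above 20 is a minor slip, since the intended cut-off is clear.

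**What to change.** In the Eligibility criteria and the Adverse symptoms paragraph, state that an SSQ score above 20 ends IVR exposure only; that the participant is still invited to the post-intervention and 3-month assessments and is analysed as randomised; and that only withdrawal of consent ends data collection. Change the cut-off in the Adverse symptoms paragraph to >20. If anyone has already been withdrawn on this rule, invite them to whichever assessments are still due, provided their consent stands.

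The cost is a short amendment and at most two already scheduled visits for each affected participant. The sample size does not change.

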### Sample size calculation

Sample size estimation was performed using G*Power software (version 3.1.9.7), taking the primary outcome variable, balance, assessed by the Mini-BESTest scale as the reference. Although the hypothesis anticipates superior outcomes for the experimental IVR intervention compared to the control condition, a two-tailed alternative hypothesis was adopted to maintain a conservative statistical approach. The calculation was based on a repeated measures design involving two groups and three time points, but specifically on the expected difference between groups at the post-intervention time point assuming a moderate effect size (d = 0.71), a significance level of 0.05, and a statistical power of 80%**.** Although the study includes follow-up measurements, this approach provides a conservative estimate expected to offer adequate power for comparisons at follow-up. Because the sample size calculation relies on the expected between‑group difference at the post‑intervention time point, assumptions about the correlation between repeated measurements will not be necessary. Under these conditions, the required sample size was determined to be 50 participants, with 25 allocated to each group. To accommodate an estimated 10% attrition rate, the final target sample was increased to 56 participants (28 per group).

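### The stated inputs (two-tailed, alpha 0.05, d = 0.71, 80% power, one post-intervention comparison) do not give 25 per arm: they give 69% power at 25, and 80% needs 33 per arm

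*Protocol article*

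**What the plan says.** All the inputs are in the protocol article, section Sample size calculation. The primary outcome, the Mini-BESTest, is the reference variable and G*Power 3.1.9.7 is the software.

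- Sidedness: "a two-tailed alternative hypothesis was adopted to maintain a conservative statistical approach".
- Effect, alpha and power: "assuming a moderate effect size (d = 0.71), a significance level of 0.05, and a statistical power of 80"%.
- Comparison: a repeated-measures design with two groups and three time points is mentioned, "but specifically on the expected difference between groups at the post-intervention time point".
- Correlation: because of that choice, "assumptions about the correlation between repeated measurements will not be necessary".
- Result: "the required sample size was determined to be 50 participants, with 25 allocated to each group", raised to 56 (28 per group) for 10% attrition.
- Follow-up: "this approach provides a conservative estimate expected to offer adequate power for comparisons at follow-up".

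The section Allocation and blinding fixes 1:1 allocation. The section Statistical analysis names the test that matches the calculation: independent-samples t-tests between groups at each time point, with Mann–Whitney U as the alternative.

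**The concern.** A two-group comparison of means at a single time point is fully determined by sidedness, alpha, power, standardised effect and allocation ratio. The section gives all five, so its answer can be checked without any outside figure. The stated 25 per arm is well below what a two-sided calculation with d = 0.71 should return.

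This is the power statement for the primary outcome. If the type II error under the stated assumptions is about 31% rather than 20%, a reader of a null result will take it as stronger evidence against the assumed effect than it is. The reassurance about follow-up rests on the same number.

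**Working it through.** **Inputs.** d = 0.71, alpha = 0.05, two-tailed, target power 0.80, no correlation (Sample size calculation); 1:1 allocation (Allocation and blinding); independent-samples t-test (Statistical analysis).

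**Formula.** With n per arm, the t statistic has df = 2n − 2 and noncentrality δ = d × √(n/2). Two-sided power is P(|T| > t at the 0.975 quantile), with T noncentral t.

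**1. The plan's own figure, as described.** n = 25: df = 48, δ = 0.71 × √12.5 = 2.510, critical t = 2.011. Power = **69.1%**, against the stated 80%. The figure does not reproduce.

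**2. Other sample sizes, two-sided.**

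| n per arm | δ | Power |
|---|---|---|
| 25 (stated requirement) | 2.510 | 69.1% |
| 28 (full target, no dropout) | 2.657 | 74.2% |
| 32 | 2.840 | 79.8% |
| 33 | 2.884 | 81.1% |

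So 80% power needs **33 per arm, 66 evaluable**. The normal approximation, n = 2 × (1.960 + 0.842)² / 0.71² = 31.1, gives 32 per arm (64). The choice of approximation does not explain the gap to 50.

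**3. What 25 per arm can detect.** Solving for 80% two-sided power at n = 25 gives **d = 0.81**.

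**4. The attrition step.** 50 / 0.9 = 55.6, and 25 / 0.9 = 27.8 per arm. Rounding up gives 56 and 28. This step is correct.

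**5. Routes that do arrive at about 50.** The settings are not shown, so these are candidates only.

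- *One-tailed test.* Normal approximation: 2 × (1.645 + 0.842)² / 0.71² = 24.5, so 25 per arm. Noncentral t: 79.7% at 25 and 81.1% at 26, so 26 per arm (52 in total). This contradicts the two-tailed statement.
- *Repeated-measures ANOVA, between-groups factor.* Effect f = 0.71 / 2 = 0.355; noncentrality λ = N × f² × m / (1 + (m − 1)ρ) for m measurements with correlation ρ.
  - Three measurements, ρ = 0.65: λ = 50 × 0.126 × 3 / 2.30 = 8.22, power 80.2% at N = 50.
  - Two measurements, ρ = 0.5: λ = 50 × 0.126 × 2 / 1.5 = 8.40, power 81.1% at N = 50, and 79.4% at N = 48.
  - Both need a correlation, and the section says none was needed. Both also size an average over time points rather than the post-intervention difference alone.
- *Mann–Whitney U.* At its efficiency relative to the t-test (3/π under normality, 0.864 at worst), two-sided 80% power needs 34 to 38 per arm. This moves further from 25.

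**6. Follow-up.** A single unadjusted comparison at follow-up with the same d and the same 25 evaluable per arm has the same 69.1% power. It has less if the effect shrinks or more participants are lost.

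**The case against.** **The calculation may have been a repeated-measures one.** The section does mention two groups and three time points, and this route fits 50 at least as well as the one-tailed route does. But it then needs a correlation, which the section says it did not use, and a comparison other than the one the section names. The objection changes which sentence is wrong, not whether one is.

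**A reader might infer that a one-tailed test was run and reported as two-tailed.** The documents do not establish this. No settings are given, the t-based one-tailed answer is 26 per arm rather than 25, and other routes reach 50. It is one possible explanation.

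**A reader might infer that the trial itself has only 69% power.** That goes too far. The figure belongs to the unadjusted t-test on which the section says it sized. The section Statistical analysis also plans a linear mixed model over three time points, whose power depends on a within-person correlation that the article does not give. The mixed model cannot rescue the stated 80% either, since the calculation disclaims that input.

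**A reader might infer that Bonferroni lowers the power further.** The article attaches Bonferroni to post hoc comparisons after mixed-model effects and mentions it again beside the within-group nonparametric tests. It names no adjustment for the between-group tests at each time point, so no reduced power can be derived for them.

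**The word conservative is partly right.** Choosing a two-tailed over a one-tailed test is conservative, and that description stands. Only its second use, for the estimate and follow-up power, is unsupported.

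**Conclusion.** The point holds as a failure of the stated inputs to yield the stated sample size. Under those inputs, 25 per arm gives 69% power instead of 80%, and 28 per arm without dropout gives 74%. The requirement is 66 evaluable rather than 50, a shortfall of 16, or 16/66 = 24% of what is needed. The result assumes a two-sample t-test with equal arms, equal variances and d = 0.71; a rank test would widen the gap slightly. It does not depend on knowing how the error arose, and the documents do not settle that. The statement that the estimate is conservative and adequate for follow-up fails with it, because 69% is below the plan's own target even for one unadjusted comparison. The attrition inflation is correct.

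**What to change.** In the section Sample size calculation:

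1. State the exact G*Power test and every input used (test family, sidedness, effect-size measure, number of measurements and correlation, if any).
2. If the calculation was meant as described, replace the power statement with: *With 25 evaluable participants per arm, an unadjusted two-sided 5% comparison at post-intervention has 69% power for d = 0.71 and 80% power for d = 0.81.*
3. If a correlation was in fact assumed, state its value, and remove the sentence saying that none was needed and the statement that sizing rests on the post-intervention difference alone.
4. Remove the claim that the estimate is conservative and gives adequate power at follow-up. Keep the description of the two-tailed choice.

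The cost is a few sentences and, under item 2, a less favourable power statement. No extra participants are asked for; the section Study design expects recruitment to end in February 2026.

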### Intervention

A total of 8 face-to-face physical therapy sessions will be conducted over a 4-week period, with a frequency of 2 sessions per week and a follow-up 3 months after the intervention. Each session will last 40 minutes, divided into 2 separate 20-minute segments.

The first part of the intervention will be the same for both groups and will consist of a usual physical therapy session based on the Modified Fitness Counts (mFC) exercise program [33], during which participants will perform 15 repetitions of eccentric exercises targeting antigravity muscle groups, including the trunk, knee flexors and extensors, and hip extensors. Exercises will be performed either in a sitting or standing position, depending on the specific muscle group involved. Movements will be executed at a slow contraction velocity to minimize compensatory strategies. The duration of the eccentric phase will be a maximum of 3 seconds and 1 second for the isometric hold [34].

The second part of the treatment protocol will differ according to group allocation. In the experimental group, the second part of the intervention will consist of a personalized static and dynamic balance physical therapy program delivered through IVR using the Oculus Quest 2 VR headset and FisioVR^®^ software (Abaco Digital, Zaragoza, Spain). This program includes a series of 360º spherical images depicting urban environments familiar to the participants, designed to simulate realistic scenarios in which various postural activities are performed. The immersive setting allows participants to move and explore the virtual environment with greater freedom, engaging in both static and dynamic balance mechanisms. Throughout the intervention, the physical therapist will continuously monitor on a computer the exact content the patient is viewing in the VR environment.

At the beginning of each session, participants will be seated comfortably while the VR headset is fitted and adjusted to ensure optimal focus and comfort. A brief familiarization phase will follow, during which participants will identify objects and landmarks within the environment to confirm adequate visual clarity. Throughout this initial phase, subjective feedback regarding visual distortion, discomfort, or disorientation will be collected to monitor adaptation to the immersive environment. This phase will last 3 minutes [35].

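### Sizing on one post-intervention comparison gives no basis for calling power at the 3-month follow-up conservative or adequate

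*Protocol article*

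**What the plan says.** Under Sample size calculation, the protocol article bases the number of patients on the between-group difference in Mini-BESTest at the post-intervention visit, "assuming a moderate effect size (d = 0.71), a significance level of 0.05" and 80% power. On sidedness it says that "a two-tailed alternative hypothesis was adopted to maintain a conservative statistical approach". The result is 25 per group, raised to 28 for 10% attrition.

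Two further statements follow from this choice. One is that "assumptions about the correlation between repeated measurements will not be necessary". The other is that "this approach provides a conservative estimate expected to offer adequate power for comparisons at follow-up". The section gives no effect size, power or significance level for follow-up.

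The Intervention section places that visit as "a follow-up 3 months after the intervention", which itself lasts 4 weeks and 8 sessions. The Statistical analysis section plans a linear mixed model over three time points, and of its findings says: "Significant main or interaction effects will be further explored through Bonferroni-adjusted post hoc comparisons". In a separate paragraph it adds: "Between-group differences at each time point will be examined using independent-samples t-tests", with Mann–Whitney as the alternative for non-normal data.

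**The concern.** A sample size is conservative for a second comparison only if that comparison is easier to win than the one used for sizing. Nothing stated makes the 3-month comparison easier. It has the same two arms and at best the same number of patients. The per-visit t-test does not use baseline. The visit falls three months after a short program has ended. The sentence therefore needs the whole d = 0.71 to persist, and the article does not state or support that assumption.

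The stake is how the 3-month result is read. If the protocol has declared power adequate, a non-significant difference at follow-up invites the reading that the benefit has been lost. With the power the design actually has, such a result would often be inconclusive.

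**Working it through.** **Inputs.** From Sample size calculation: d = 0.71, two-sided alpha 0.05, 80% power, 25 per arm evaluable, 28 per arm randomised. From Allocation and blinding: 1:1. From Statistical analysis: an independent-samples t-test at each visit. The protocol gives no retained fraction of the effect, no Bonferroni count for these tests and no correlation; all three are assumed below and shown as ranges.

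**The plan's own figure.** By the normal approximation, n per arm = 2(z₁₋α/₂ + z₀.₈)²/d².
- Two-sided: 2(1.960 + 0.842)²/0.71² = 31.1, so 32 per arm. The t-test needs 33 (66 in total).
- One-sided: 2(1.645 + 0.842)²/0.71² = 24.5, so 25 per arm.

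The stated 50 therefore fits a one-sided test, although a two-tailed one is declared. The attrition step is right: 50/0.9 = 55.6, so 56. The error in N is a separate matter. It is kept apart here by also showing 33 per arm.

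**Follow-up power of the per-visit t-test.** Power is the probability that a noncentral t with 2n − 2 degrees of freedom and noncentrality d√(n/2) falls outside ±t₀.₉₇₅. At 25 per arm with the full effect, the noncentrality is 0.71 × √12.5 = 2.510 and the critical value (48 df) is 2.011, so power is 69.1%.

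| Per arm | 100% kept (d = 0.71) | 90% (0.639) | 75% (0.5325) | 50% (0.355) |
|---|---|---|---|---|
| 25 | 69.1% | 60.0% | 45.4% | 23.3% |
| 28 (no dropout) | 74.2% | 65.1% | 49.9% | 25.7% |
| 33 (sized for two sides) | 81.1% | 72.5% | 56.8% | 29.5% |

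The 100% column is also the post-intervention power, because the test and the inputs are the same.

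**Effect needed for 80%.** About d = 0.81 at 25 per arm (0.81/0.71 = 1.14, or 14% larger than assumed post-intervention) and about 0.76 at 28 per arm (7% larger).

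**If Bonferroni also covered these tests.** At 25 per arm with the full effect, power is 58% for an assumed 2 comparisons (alpha 0.025) and 52% for 3 (alpha 0.0167).

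**If the analysis used baseline.** Adjusting for baseline with correlation ρ turns d into d/√(1 − ρ²). At 25 per arm, full effect and alpha 0.05, power is 73%, 81% and 93% at ρ = 0.3, 0.5 and 0.7. A change-from-baseline contrast uses d/√(2(1 − ρ)) and gives 69% at ρ = 0.5 and 89% at ρ = 0.7.

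**Precision.** The 95% CI half-width for the difference at 25 per arm is 2.011 × √(2/25) = 0.57 SD.

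**The case against.** Four objections carry weight.

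- A reader might infer that follow-up power can never exceed post-intervention power. The article does not support that. It states no follow-up effect, and if the effect grew by 20%, power at 25 per arm would be 83.9%. The bound holds only if the standardised effect does not grow and no more patients are observed.
- A reader might take Bonferroni as settled for the per-visit t-tests. The article attaches it to the mixed-model and non-parametric post hoc comparisons. A general remark on multiple testing could be read more widely, but no number of comparisons is given. The Bonferroni figures are therefore conditional, and the point does not depend on them.
- The mixed model comes before the t-tests, and its handling of baseline may be set out elsewhere. Baseline adjustment gains power at any non-zero correlation, so it would be wrong to say that only a change score with a high correlation could rescue the claim. However, that gain needs a correlation, and the sizing paragraph says none is needed, so its claim cannot rest on one.
- The 69% comes from the N problem as much as from follow-up: at 33 per arm with the full effect kept, power is 81% and the claim of adequacy would hold. This is correct. It still leaves one percentage point of margin, which 10% waning more than removes.

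It can also be said that the sentence is hedged, that no passage says a non-significant 3-month result would be read as lost benefit, and that effect sizes with 95% confidence intervals and reference to clinically important differences are already planned for the primary outcome. These limit the harm, but they do not make the power statement true.

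**Conclusion.** The point holds in a limited form. The protocol claims a property for the follow-up comparison that its stated design does not have. For the planned per-visit t-test at 25 per arm, power is 69% with the whole effect retained, and 60% to 23% with 90% to 50% retained. Correcting N to 33 per arm brings full-retention power to 81% but leaves 72.5% after 10% waning, so a corrected N would not make the sizing conservative for follow-up either.

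The figures rest on d = 0.71 post-intervention, the unadjusted t-test, alpha 0.05 and assumed retention fractions. The documents do not show that the effect will wane or that follow-up power is inadequate under every analysis. A baseline-adjusted analysis with a sufficient correlation could reach 80% with full retention. What is missing is any stated assumption under which the claim is true. The matter is worth correcting but does not threaten the primary post-intervention comparison.

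**What to change.** In Sample size calculation, delete the sentence claiming a conservative estimate with adequate power at follow-up. In its place:

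- State that the trial is sized for the post-intervention contrast only.
- Give follow-up power at the planned number of patients under declared assumptions: the fraction of the effect retained, the alpha used (and whether Bonferroni covers the per-visit tests) and, if the analysis adjusts for baseline, the correlation. If N is revised for the two-sided test, compute these figures at the revised N.
- Label the 3-month Mini-BESTest comparison as secondary and interpret it from the estimate and 95% CI already planned (half-width about 0.57 SD at 25 per arm).
- State that a non-significant 3-month result will be called inconclusive, not evidence that the effect is lost.

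The cost is a less favourable power statement and a more cautious status for the 3-month comparison. This point requires no extra patients, visits or procedures.
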